### Data monitoring

Adverse events (AE) are defined as any undesirable experience occurring to a subject during the study, whether or not considered related to undergoing a dietary treatment. All adverse events observed by the researchers or reported by the participants will be recorded. A serious adverse event (SAE) is an event that 1) results in death; 2) is life threatening (at the time of the event); 3) requires hospitalization or prolongation of existing inpatients’ hospitalization; 4) results in persistent or significant disability or incapacity; 5) is a congenital anomaly or birth defect; 6) may jeopardize the participant or may require an intervention to prevent one of the outcomes listed previously. All SAEs will be communicated to the coordinating investigator ([name]), who will be responsible for reporting this through the web portal ToetsingOnline to the accredited METC (IRB) that approved the protocol. Reporting of SAEs that are life threatening or result in death, will be reported not later than 7 days after first knowledge of the SAEs in a preliminary report. The final report will be completed no later than 8 days after the preliminary report. All AEs will be monitored until they are diminished or until they reached a stable situation. Follow up may require: 1) medical procedures; 2) additional tests; 3) referral to a general physician or medical specialist. SAEs need to be reported till end of study within the Netherlands, as defined in the protocol.

A safety review will be performed by the safety review board (SRB), with the aim to safeguard the interests of trial participants, assess the safety and efficacy of the interventions during the trial, and monitor the overall conduct of the clinical trial. The members of SRB receive and review the progress and accruing data of this trial and provide advice on the conduct of the trial to the Trial Steering Committee. The SRB informs the Chair of the steering committee if, in their view: (i) the results are likely to convince a broad range of clinicians, including those supporting the trial and the general clinical community, that one trial arm is clearly indicated or contraindicated, and there is a reasonable expectation that this new evidence would materially influence patient management; or (ii) it becomes evident that no clear outcome will be obtained.

Specific roles of the SRB: Interim review of the trial’s progress including updated figures on recruitment, main outcome and safety data.

Specific aspects:
monitor recruitment figures and losses to follow-upmonitoring evidence for treatment differences in the main efficacy outcome measuredecide whether to recommend that the trial continues to recruit participants or whether recruitment should be terminated either for everyone or for some treatment groups and/or some participant subgroups

The SRB meets before the trial starts, to discuss the protocol, the trial, any analysis plan, future meetings, and to have the opportunity to clarify any aspects with the principal investigators. The SRB will meet at least yearly, interim analyses will be conducted when 50% of the participants has completed the first 5 weeks of the study. Interim analyses will include the percentage of responders in each dietary treatment and adverse effects reported. Stopping rule: when only 5% (instead of 42%) of participants are regarded responders to the dietary treatments after having included 50% of the participants, we will terminate the study. It is then unlikely that the dietary treatment-trajectory will be as effective and cost-effective as CAU. At the end of the trial there will be a meeting to allow the SRB to discuss the final data with the principal trial investigators and give advice about data interpretation.

Composition: [name], pediatrician at the RadboudUMC. Role: head of safety review board. [name], statistician at the RadboudUMC. Role: statistical analyses. [name], senior researcher at Karakter Child and Adolescent Psychiatry. Role: statistical analyses.

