To address these issues, the ‘Treatment of ADHD with Care as usual versus an Elimination diet’ (TRACE) study has been developed. This is the first RCT (two armed, 50:50 ratio) to determine the short- and long-term effectiveness and cost-effectiveness of an ED compared to an active control group (a healthy diet). Care As Usual (CAU) is included as a comparator arm. During the initial 5 weeks of the study, participants receiving a dietary treatment are not allowed to start any other treatment. Also, medication prior to the dietary treatment has to be discontinued no later than 1 week before start of the diet. The study will examine effects on both ADHD and emotion dysregulation, given that an ED showed equal effects on ADHD and its common comorbidity Oppositional Defiant Disorder (ODD) (i.e. children with ODD are more likely to experience emotion dysregulation problems) [14]. We will substantially improve upon previous studies by comparing an ED with a healthy diet (based on the World Health Organization (WHO) guidelines), comparing the two dietary treatments with CAU, examining the short- and long-term effects (i.e. after 5 weeks and 1 year) and cost-effectiveness, measuring the nutritional quality of the consumed diets and including blinded and objective measurements.

The primary objective of the TRACE study is to quantify the short-term (after 5 weeks) effectiveness in reducing ADHD and emotion dysregulation symptoms of an ED compared to an active control group (a healthy diet) in children aged 5–12 years with ADHD: we assume that the ED is more effective than the healthy diet. Secondary, the study aims at examining the long-term (after 1 year) effects in reducing ADHD and emotion dysregulation symptoms. Moreover, the study aims at examining the short- and long-term effects of an ED compared to an active control group (a healthy diet) in reducing secondary outcome measures related to ADHD such as cognitive outcomes, motor activity and sleep pattern. In addition, the study aims to identify potential moderators and mediators (e.g. socioeconomic status (SES), ethnicity, comorbidity) of the short- and long-term response to dietary treatments, and to examine the nutritional quality of the attained diet and health of children treated with a dietary treatment compared to CAU. Finally, the study aims to examine the cost-effectiveness of the dietary treatments compared with CAU.

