### Interventions

In both dietary groups, weekly contacts with the dietician (via telephone or video calls) are scheduled to keep the participant and family motivated, respond to questions and assess adherence and nutritional quality. After 2 weeks, researchers contact the family to evaluate experiences with the diet so far. To keep track of daily changes in behavior, parents evaluate the severity of hyperactivity/impulsivity, attentional, physical and emotional problems on a 5-point scale (ranging from *1 no problems* to *5 severe problems*) every day (during the first 5 weeks and during the re-introduction phase of the ED). Dieticians discuss this daily assessment on the four subscales during their weekly contacts with parents. This daily assessment is specifically developed for the present study. To facilitate feasibility and adherence to the diet, parents receive examples of menus, recipes, shopping lists and advice for situations outside their home (e.g. parties).

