Subsequently: sorbic acid, sulphites, glutamates/glutamic acid, artificial colorings and further examination (if needed) of products that child responded to by re-introducing products again		

During the reintroduction phase, parents have contact with a dietician every 2 months to identify foods that trigger ADHD symptoms in their child, to give mental support and to answer questions about the diet. In addition, depending on the parents’ needs, the researchers can provide mental support and advice to the parents via telephone. Furthermore, all foods and/or food components that have to be avoided are registered. Eventually this phase leads to a consolidated dietary advice about the specific foods to be avoided, while maintaining an otherwise normal diet. Participants who drop-out at any time can switch to CAU.

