##### Physical measurements

Blood pressure, heart rate, height, weight, sleep problems and somatic complaints are routinely monitored at every visit as part of standard clinical care. Sleep problems will be examined using a 5-item questionnaire (answered with ‘yes’ or ‘no’) used in standard clinical care assessing problems with falling asleep, maintaining sleep and total amount of sleep compared to children of the same age. Somatic complaints (e.g. headache, nausea) will be assessed using the frequently used Pittsburgh side-effects rating scale (translated to Dutch) [41]. The 18 items can be answered on a 4-point scale ranging from 0 (*none*) to 3 (*severe*).

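### Unsolicited adverse-event counts are liable to unequal ascertainment: only continuing elimination-diet families keep a daily rating after week 5, and none is described for care as usual

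*Protocol article*

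**What the plan says.** Under Data monitoring, the protocol article defines an AE as any undesirable experience during the study and states: "All adverse events observed by the researchers or reported by the participants will be recorded". It describes no AE questionnaire put to all arms on a common schedule. The planned interim look is described as follows: "Interim analyses will include the percentage of responders in each dietary treatment and adverse effects reported". The same section lets the safety review board (SRB) advise that recruitment end for some treatment groups.

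Under Interventions, in the two diet groups "parents evaluate the severity of hyperactivity/impulsivity, attentional, physical and emotional problems on a 5-point scale", and this is done "every day (during the first 5 weeks and during the re-introduction phase of the ED". The stated purpose is "To keep track of daily changes in behavior", and dieticians discuss the ratings at their weekly contacts. No such rating is described for CAU.

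The article also plans a structured measure. Under Physical measurements, somatic complaints "will be assessed using the frequently used Pittsburgh side-effects rating scale". Table 3 places that scale at T0, T1, T2, T3 and T4, and places weight, height, blood pressure and heart rate at T0, T1 and T4. The Measurements CAU section lists what CAU families are spared, and neither the scale nor these measurements are on the list.

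**The concern.** When AEs enter the record only if someone mentions or notices them, an arm asked more often can record more events at the same true rate. Here the amount of asking about physical problems is set by the design and differs by arm. The two diets are alike through week 5. After that, only ED families who go on to reintroduction are asked daily, and CAU families are not described as being asked daily at all. Parents, researchers and dieticians all know the allocation (Randomization section), so nothing in the conduct of the trial would even this out.

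At stake is the reading of harms. Reported adverse effects go to the SRB at the interim look. That look is triggered when half the participants have completed week 5. The trial was registered in October 2015 and recruitment was expected to run to December 2020, so many early participants could be well past week 5 by then. The SRB also meets at least yearly. An excess of ED reports after week 5 could be taken for an excess of harm.

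**Working it through.** The article gives no AE rate or ratio to reproduce. Two checks are possible: how unequal the scheduled rating is, and what that could do to counts under stated assumptions.

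**1. Scheduled rating days** (Interventions section; Table 1; 365/12 = 30.42 days per month)

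- Weeks 1-5, both diets: 5 × 7 = 35 days.
- ED reintroduction: 3 months + 2 weeks + 8 days + 2.5 months + 2.5 months = 8 × 30.42 + 14 + 8 = 265.3 days. Table 1 gives approximate periods, and the text allows up to 12 months.
- Totals: ED family completing all phases, 35 + 265.3 ≈ 300; HD 35; CAU 0.

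**2. Share of ED follow-up affected.** Only families who continue keep the later rating. Let f be the share who continue and complete reintroduction. The share of ED's 12 months under daily rating with no HD counterpart is f × 265.3/365 = 0.727f. The article gives no continuation rate, so responder proportions are used as stand-ins:

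- f = 0.42 (responder figure in the stopping rule): 31%
- f = 0.60 (Table 4 scenario 2, full plus partial, 15% + 45%): 44%
- f = 0.75 (Table 4 scenario 1, 20% + 55%): 55%

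**3. Illustration with equal true AE rates in all arms.** Let d1 be the chance that an event is recorded while a daily rating is kept, and d0 the chance otherwise. Both are assumptions. Expected recorded events are proportional to:

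- ED = 35·d1 + f·265.3·d1 + (330 − f·265.3)·d0
- HD = 35·d1 + 330·d0
- CAU = 365·d0

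Example, f = 0.42, d1 = 0.9, d0 = 0.7: ED = 31.5 + 100.3 + 153.0 = 284.8; HD = 31.5 + 231.0 = 262.5; ED/HD = 1.08.

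Ratios over 12 months:

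| f | ED/HD at 0.9/0.7 | ED/CAU at 0.9/0.7 | ED/HD at 0.9/0.5 | ED/CAU at 0.9/0.5 |
|---|---|---|---|---|
| 0.25 | 1.05 | 1.08 | 1.14 | 1.22 |
| 0.42 | 1.08 | 1.11 | 1.23 | 1.32 |
| 0.75 | 1.15 | 1.18 | 1.41 | 1.51 |
| 1.00 | 1.20 | 1.24 | 1.54 | 1.66 |

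HD/CAU over 12 months is 1.03 at 0.9/0.7 and 1.08 at 0.9/0.5. If the rating adds no reports (d1 = d0), every ratio is 1.00.

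**4. The two periods apart**

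- Weeks 1-5: ED/HD = 35·d1/(35·d1) = 1.00 whatever the detection values. Either diet against CAU = d1/d0 = 1.29 or 1.80.
- After week 5: ED/HD = 1 + f × (265.3/330) × (d1/d0 − 1). At f = 0.42 this is 1.10 at 0.9/0.7 and 1.27 at 0.9/0.5.

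Any imbalance between the randomized arms therefore arises entirely after week 5. Against CAU it is present from the start and affects both diets.

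**The case against.** The strongest reply is that the link from rating to AE record is inferred. The rating is described as a way of following behavior, and in reintroduction it serves to judge whether a food triggers ADHD symptoms. Nothing says that a rated physical problem becomes an AE. This stands, and it is why the point is one of liability. The inference is still reasonable: a physical problem that a parent rates as present fits the article's broad AE definition.

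A reader might go further and infer that AE counts are biased against the ED. The document does not support that, because the direction depends on the rating prompting reports and the size is unknown.

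A reader might also take the ED section's remark that "the researchers can provide mental support and advice to the parents via telephone" as a second source of imbalance. The Healthy diet section says contact frequency with dietician and researchers is similar to the ED, and dietician contact after week 5 is two-monthly in both. Only the daily rating differs.

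Three further replies have force:

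- The article plans no between-arm AE test or ratio, and its only numeric stopping rule concerns responders. The interim look nonetheless includes reported adverse effects, and the SRB may advise on single arms.
- The Background aim to examine the "health of children treated with a dietary treatment compared to CAU" is not tied to AE counts, so it cannot be said to rest on them.
- CAU children have treatment contacts of their own, of unstated frequency, and that arm is not randomized. The contrast with CAU is therefore uncertain in size and would not be a clean safety comparison in any case.

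Finally, a condensed article may leave AE tabulation to the full protocol or analysis plan. That covers missing detail. It does not cover the unequal rating schedule, which the article itself fixes.

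**Conclusion.** The point holds as a caution about unsolicited, non-serious AEs. The document fixes an unequal schedule of asking about physical problems: about 300 days for an ED family completing reintroduction, 35 in HD, none described in CAU. It combines this with AE capture that depends on observation or report. If the rating prompts reports, counts would be inflated for ED against HD after week 5, and for either diet against CAU at any time.

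The 12-month ED/HD ratio of 1.00 to 1.54 is an illustration. It rests on assumed detection values (no difference, 0.9/0.7, 0.9/0.5), on 25% to 100% of ED families continuing, on constant and equal true rates, and on Table 1's approximate periods. It is not an estimate of bias. Through week 5, the primary period, the randomized diets have the same rating and similar contact, so no ED-versus-HD problem arises there. It would also be wrong to conclude that the trial lacks a fair harm measure: one is already collected on a common schedule, and the article simply does not give it precedence over reported AEs.

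**What to change.** Make the Pittsburgh side-effects scale (T0-T4) and the physical measurements (T0, T1, T4) the main basis for between-arm harm comparisons, including the SRB's interim review of reported adverse effects. In addition:

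- Record the source of each AE: daily rating, dietician contact, visit or spontaneous report.
- Show ED-versus-HD AEs separately for weeks 1-5 and for the later period.
- Present later AEs, and all AEs against CAU, descriptively, with diary-prompted reports flagged.
- Keep serious AEs reported in full over the whole study.

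The cost is one extra AE field, some wording on harms presentation, and less weight on non-serious AE counts after week 5. No new measurement is needed. An equal schedule does not make the side-effects scale blinded, and CAU remains a non-randomized comparison, so both limits should be stated beside the results. The source field has to be filled in as AEs are recorded, because a later analysis plan cannot recover it.

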## Methods

### Participants

Families are recruited at two clinical centers in the Netherlands: Karakter Child and Adolescent Psychiatry (Nijmegen) and Triversum - GGZ-NHN Child and Adolescent Psychiatry (Alkmaar). Researchers will screen files of patients (after consent of parents and/or psychiatrists) within these centers in order to check for eligibility or psychiatrists will refer the patients to the study. In addition, participants are recruited at the national level via advertisements, newspapers, the TRACE website, flyers and social media. Moreover, general practitioners, dieticians and other psychiatric institutions act as ambassadors and collaborate in the recruitment process by referring patients to the study. At the Nijmegen site, there is a team of certified clinicians who can diagnose (if necessary) participants recruited outside the participating centers.

For eligibility, participants must meet the following criteria: ADHD diagnosis according to the DSM-5 (any presentation) and 5–12 years old at the inclusion date. Comorbidities are allowed except for eating disorders (i.e. anorexia or bulimia nervosa) and diabetes mellitus. Exclusion criteria are insufficient mastery of Dutch language in parents or children; current treatment for ADHD that cannot be discontinued; significant parent-child relationship problems requiring family therapy; unwillingness to have meat or animal food products in the diet (without these products it is impossible to achieve nutritional adequacy of the overall diet for participants in the ED group). The CAU participants need to fulfill the same inclusion- and exclusion criteria.

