### Study design

#### Randomization

Originally, the TRACE study was a three arm randomized controlled trial: participants were randomized to an elimination diet, healthy diet or CAU. However, randomization across a dietary intervention versus CAU proved not feasible. Parents usually had a strong preference towards either a dietary intervention or CAU. This resulted in an extremely slow inclusion rate, a high number of drop-outs and thereby unrepresentative groups of CAU. Therefore, after inclusion of 17 participants, the design was changed into a two arm randomized controlled trial (elimination diet vs. healthy diet) with a non-randomized comparator arm (CAU). Participants interested in a dietary intervention are randomized (50:50) to either an ED or a healthy diet with randomization within each participating center. Randomization by means of minimization is performed, including sex and age as factors, resulting in four groups. Within each group, blocked randomization is used (block size eight). The non-randomized comparator arm includes children who are being treated with CAU. Researchers disclose the group allocation to parents via a sealed envelope. Participants, researchers and dieticians are aware of treatment allocation. Researchers who will code the behavior observation (see secondary outcomes) are blinded to group allocation and time of assignment.

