#### Primary outcome

##### Respondership

Parents and teachers are invited to rate the child’s ADHD traits using the SWAN questionnaire. The SWAN consists of 18 DSM-IV-based items scored on a 7-point Likert scale ranging from 3 (*far below average*) to -3 (*far above average*) with higher scores reflecting more severe ADHD symptoms [21]. Items 1 to 9 assess symptoms of the ADHD inattentive type and items 10 to 18 assess symptoms of the ADHD hyperactive/impulsive type. The Dutch version of the SWAN questionnaire is a reliable instrument (Cronbach’s α = .87) [28, 29] and demonstrates adequate convergent and discriminant validity [28, 29]. Parents and teachers also are asked to fill out the Strengths and Difficulties Questionnaire (SDQ) to assess emotion dysregulation [30]. The SDQ Dysregulation Profile (SDQ-DP) includes fifteen items representing emotional symptoms, conduct problems and hyperactivity-inattention [31]. The items can be answered on a 3-point scale ranging from 0 (*not true*) to 2 (*definitely true*) with higher scores indicating more emotion dysregulation problems. The Dutch version of the SDQ-DP demonstrates adequate reliability (Cronbach’s α = .85) and construct and longitudinal validity [31].

To align with the evaluation of the diet after 5 weeks, response to treatment will be evaluated by assessing the change in ADHD and emotion dysregulation symptoms at T0 and T1 or T4 (i.e. SWAN inattentive scale, SWAN hyperactive/impulsive scale and SDQ dysregulation profile rated by both parent and teacher: together six scales) [32]. A 30% or more symptom decrease will be regarded as a significant response to treatment (i.e. positive value), and a 30% or more symptom increase is regarded as significant deterioration of symptoms (i.e. negative value) [9, 33]. The primary outcome variable ‘respondership’ is divided into five categories:
Full responder (significant response on both parent and teacher rated scales): all scales are ≥ − 20% AND at least one of three parent rated scales shows a ≥ 30% symptom reduction AND at least one of three teacher rated scales shows a ≥ 30% symptom reduction.Partial responder (significant response on parent or teacher rated scale):

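### One of the safety review board's two analysts of by-diet interim efficacy data is employed at a recruiting centre, so the board is not fully independent of the trial

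*Protocol article*

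**What the plan says.** The Data monitoring section gives the board three members. Two are at RadboudUMC: a paediatrician, who heads the board, and a statistician, whose role is statistical analyses. The third is a "senior researcher at Karakter Child and Adolescent Psychiatry. Role: statistical analyses".

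The Participants section states: "Families are recruited at two clinical centers in the Netherlands: Karakter Child and Adolescent Psychiatry (Nijmegen"; the only other centre listed is Triversum in Alkmaar. RadboudUMC is not listed as a recruiting centre.

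On access, Data monitoring says: "The members of SRB receive and review the progress and accruing data of this trial". It makes no exception for any member. The board's tasks include watching for treatment differences in the main efficacy outcome and deciding whether to recommend that recruitment go on, or stop for everyone or for some treatment groups. On timing: "interim analyses will be conducted when 50% of the participants has completed the first 5 weeks of the study". On content: "Interim analyses will include the percentage of responders in each dietary treatment and adverse effects reported".

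The Randomization section says: "Participants, researchers and dieticians are aware of treatment allocation". On the primary outcome, the Respondership section says: "Parents and teachers are invited to rate the child’s ADHD traits using the SWAN questionnaire". The same raters complete the SDQ.

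**The concern.** A monitoring board sees unblinded comparative results so that those running the trial need not. Here one of the people assigned to produce those results works for a centre that recruits, assesses and supports the families.

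This trial is more exposed than most. Allocation is open and the primary outcome rests on parent and teacher report. Researchers also have repeated contact with families: intake and disclosure of allocation, a call after two weeks, telephone support during reintroduction, and help with completing questionnaires. The article's Background faults earlier elimination-diet studies for unequal parental expectations and for expectation bias, and the healthy-diet arm is designed to equalise such factors. If knowledge of which diet is ahead reached staff in contact with families, it could affect how the diets are presented, and so expectation, retention and ratings. Separately, advice on whether to continue is more credible when nobody giving it is employed by a participating centre.

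**Working it through.** This is a question of governance, so the main check sets the statements side by side. A short calculation then shows how much the interim figures could reveal.

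**1. Does the text place a recruiting-centre employee at the by-diet data?**
- Employer: Karakter (Data monitoring, board composition). Karakter recruits (Participants) and, as a participating site, hosts assessments at T0, T1 and T4 (Procedures).
- Task: statistical analyses (Data monitoring).
- Data: accruing data go to the members, and the 50% interim contains responder percentages for each diet (Data monitoring).
- Timing: the interim comes when half the participants have completed five weeks, with enrolment and 12-month follow-up still under way. Respondership is assessed again at T4 (Table 3).

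Taken together, the answer is yes, by stated composition and role. It concerns 1 of 3 members and 1 of the 2 members assigned statistical analyses.

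**2. Would the by-diet figures be informative at the interim?**

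The plan's own power was reproduced first. Inputs are the Table 4 counts, 81 per diet and two-sided α = 0.05. Simulation with a Wilcoxon/Mann-Whitney test (4,000 runs), which is close to the proportional-odds score test, gives 0.994 for scenario 1 (stated 0.99) and 0.649 for scenario 2 (stated 0.64). The stated figures hold.

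For the interim, assume that participants means the diet arms (50% of 162 = 81), split about 40 per diet. Count full plus partial responders from Table 4:
- Elimination diet, scenario 1: (16 + 45)/81 = 75.3%
- Elimination diet, scenario 2: (12 + 37)/81 = 60.5%
- Healthy diet, both scenarios: (8 + 24)/81 = 39.5%

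Power for two proportions is Φ{[|p₁ − p₂| − 1.96·√(2p̄(1 − p̄)/n)] / √[(p₁(1 − p₁) + p₂(1 − p₂))/n]}, with n = 40.
- Scenario 1: p̄ = 0.574, so (0.358 − 0.217)/0.103 = 1.37, power 0.91.
- Scenario 2: p̄ = 0.500, so (0.210 − 0.219)/0.109 = −0.08, power 0.47.

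On the full ordinal scale the simulated values at 40 per arm are about 0.87 and 0.37. If the trial's main assumption is right, the by-diet percentages at half-way would probably show which diet is ahead. Under the smaller effect they would be suggestive at most.

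**3. Does the board need this member for the by-diet analysis?**
- The RadboudUMC statistician holds the same role.
- The one numerical stopping rule compares responders to the dietary treatments with a fixed 5%. It is not worded as a comparison between diets.

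**The case against.** The strongest reply is that the pathway to bias largely exists already. Researchers know the allocation. Each child's response is evaluated after five weeks, and the advice to families follows from it. Site staff can therefore form a view of each diet case by case, whoever sits on the board. This stands: it means the added risk from one board member cannot be separated from that background, and changing the board would not remove the background. It does not answer the point on independence, because an aggregated comparison by arm carries more than individual impressions, and the recommendation on continuing is a separate matter.

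Several stronger readings are tempting and are not supported:
- *Results reach the people who recruit and rate.* No passage says this member meets, recruits or assesses families, or passes results on. Parents and teachers rate the primary outcome, and the observational measure is protected: "Researchers who will code the behavior observation (see secondary outcomes) are blinded to group allocation and time of assignment".
- *The member has a vote on stopping.* No voting procedure is described. The board advises the steering committee, and this member shares in that advice.
- *By-diet results are seen at every look.* They are specified only for the 50% interim. The yearly meetings have a general remit.
- *About 81 children would still be untreated.* The figure 162 − 81 = 81 is an upper bound under the diet-arms reading, because some of the second half will already be on a diet. If participants includes usual care, half of 162 + 60 = 222 is 111, and the number on each diet is not fixed.
- *There is no firewall.* Closed sessions and confidentiality rules are commonly left to a board charter or full protocol, which are not shown. Their absence from the article is not the finding. The finding is the composition and role that the article does state.

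It is also fair that a second analyst may be there to cross-check. The article does not say how the two divide the work.

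**Conclusion.** The point holds as a lack of independence in the stated composition of the board. An employee of one of the two recruiting centres is assigned to analyse accruing efficacy data, including responder percentages by diet at the 50% interim, and takes part in the advice on whether recruitment continues. The trial is open-label and still enrolling and following families at that time.

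No disclosure is shown. Any effect on the primary outcome would be indirect, and its size cannot be derived from the document. Sample size, α and power are unaffected. The correction is worth making because it is cheap and the trial is designed to limit expectation effects, but the point does not call the analysis into question.

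The conclusion assumes that the role and access are as the article words them. The statement that the interim is informative further assumes about 40 children per diet and the Table 4 distributions.

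**What to change.** In the board composition and interim text of Data monitoring, state that by-diet interim tables are prepared and seen only by the statistician and the paediatrician, both from outside the listed recruiting centres. State also that the Karakter member sees only data pooled over diets (recruitment, losses to follow-up, adverse events) and takes no part in the recommendation on stopping. The alternative is to replace that member with someone from neither centre. If the 50% interim has already taken place, record who saw the by-diet results.

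The first option needs no extra staff or data, because a second statistician already holds the role. The cost is that the by-diet analysis loses a second analyst who might have cross-checked it. Replacement avoids that loss but means finding a new member.
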